## A priori plans for data analysis for each objective

### Objective 1 (Evaluate differences between PASS and TAU in improving service utilization and child health outcomes)

To evaluate changes in service utilization, we will examine between-group changes in the proportion of children receiving mental health services (i.e., outpatient mental health therapy, school mental health services and special education services, and psychotropic medication) from pre-treatment to post-treatment to follow-up using the McNemar test. To evaluate the effect of intervention on child outcomes, a mixed effects model with repeated measures (MMRM) will be the general analytical approach employed. The model will examine intervention effects across four time points (baseline, mid-treatment [parent report of homework performance and behavior compliance only], post-treatment, follow-up). Data for all participants randomized to treatment condition will be included in the analytic model, consistent with an intent-to-treat (ITT) approach. Mixed effects models will estimate within-subject effects by time and between-treatment effects, as well as the interaction of time by treatment. A significant time by treatment interaction will indicate that one treatment is superior to the other. MMRM will include the fixed categorical effects of treatment, time, randomization stratification factor (medication status and primary care practice), and treatment-by-time interaction as well as covariates as indicated. Within-participant error variance–covariance will be assumed to be an unstructured matrix. Point estimates and confidence intervals for the mean change in outcomes for each treatment group as well as the difference in the estimated mean change between groups will be calculated.

Most of the outcome domains examined under Objective 1 include two measures. For example, there are two primary outcome measures – parent report of homework problems and parent report of behavior problems. In addition, ADHD symptoms will be assessed by parent report of inattention and hyperactivity-impulsivity symptoms. Because each domain generally will be assessed using two measures, tests of significance within each outcome domain will be examined using an adjusted *p* value. We have elected to use the conservative Bonferroni approach, and therefore will use a p value of 0.05/2 = 0.025. As indicated, analyses of measures completed by teachers will be underpowered. We will conduct these analyses using a* p* value of 0.05, but the primary focus will be on evaluating the magnitude of the effect size.

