**Method:**

Three hundred participants will be randomly assigned to PASS or TAU. Participants include children ages 5 to 11 who have ADHD and are from economically marginalized families. PASS is a personalized, enhanced behavioral intervention that includes evidence-based behavior therapy strategies and enhancements to promote family engagement, increase caregiver distress tolerance, and provide team-based care to improve academic and behavioral functioning. TAU includes services offered by primary care providers and referral for integrated behavioral health or community mental health services. Outcomes will be assessed at mid-treatment (8 weeks after baseline), post-treatment (16 weeks), and follow-up (32 weeks) using parent- and teacher-report measures of service use, child academic, behavioral, and social functioning, parenting practices, family empowerment, and team-based care. Mixed effects models will examine between-group differences at post-treatment and follow-up. Analyses will examine the mediating role of parenting practices, family empowerment, and team-based care. Subgroup analyses will examine differential effects of intervention by child clinical characteristics and socioeconomic factors.

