### Study objectives

The study has four objectives. The first objective is to evaluate differences between PASS and TAU in improving utilization of ADHD services and patient-centered outcomes for children with ADHD from economically marginalized families at post-treatment (16 weeks after baseline) and follow-up (32 weeks after baseline). We hypothesized that, compared to TAU, families in PASS will show greater use of services for ADHD, and children in PASS will demonstrate greater improvements in academic performance, behavior compliance, interpersonal competence, life satisfaction, and ADHD symptoms.

Second, we will compare PASS and TAU on parenting practices, caregiver sense of empowerment to navigate systems of care, and caregiver perceptions of the quality of team-based care. It is hypothesized that, compared to TAU, families in PASS will show a greater reduction in negative parenting practices, an improvement in their sense of empowerment in being able to navigate care delivery systems, and an increase in their perceptions of team-based care. Third, we will explore whether changes in caregiver processes (parenting practices, caregiver sense of empowerment, perceptions of team-based care) mediate the effect of intervention on child outcomes. Finally, we will explore the heterogeneity of treatment effect for families of varying levels of socioeconomic resources, caregivers with varying levels of stress and health literacy, medicated versus unmedicated children, and children with varying levels of mental health symptom severity at baseline.

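### The superiority rule rests on a 3-df treatment-by-time interaction that week 8 alone can make significant, while the objective concerns weeks 16 and 32

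*Protocol article*

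**What the plan says.** In the Objective 1 analysis section the child outcomes are analysed with a repeated-measures mixed model (MMRM). Time enters as a category: "MMRM will include the fixed categorical effects of treatment, time, randomization stratification factor". The section adds: "The model will examine intervention effects across four time points". The mid-treatment visit applies only to parent-reported homework performance and behavior compliance, which are the two primary outcomes.

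The decision rule is one sentence: "A significant time by treatment interaction will indicate that one treatment is superior to the other". It names no visit, contrast or direction. The section also plans estimates and confidence intervals for each arm's mean change, and says that "the difference in the estimated mean change between groups will be calculated". It does not make that difference the criterion or name its visit. For multiplicity, each outcome domain generally has two measures, and the authors "therefore will use a p value of 0.05/2 = 0.025".

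The Study objectives section places the comparison at 16 and 32 weeks, gives neither priority, and states a direction: "children in PASS will demonstrate greater improvements in academic performance, behavior compliance, interpersonal competence, life satisfaction, and ADHD symptoms". The abstract says: "Mixed effects models will examine between-group differences at post-treatment and follow-up". The Sample size section claims 85% power for 0.30 SD with 240 evaluable participants.

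**The concern.** The stated rule and the stated question differ. The question is whether PASS does better than TAU at weeks 16 and 32. The rule asks whether the arm difference varies over baseline and weeks 8, 16 and 32. Week 8 is not in the objective, yet it counts as much in the test as either visit that is.

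Two things are at stake. First, a mid-treatment difference that has gone by week 16 would meet the written criterion for superiority. Such a result is not a false positive for the interaction, but it does not answer the objective. Second, a 3-df test spreads its power over patterns of no interest, so a real and sustained benefit is harder to establish than the Sample size section suggests.

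**Working it through.** **Inputs.** From Sample size: 240 evaluable participants, correlation 0.3, detectable effect 0.30 SD, expected range 0.35 to 0.60 SD. From Assignment of interventions: 1:1 allocation, hence n = 120 per arm. From the Objective 1 analysis: four visits, categorical time, alpha 0.025 per primary outcome. Assumed, because not stated: two-sided tests, complete data in the 240, normal approximation with known covariance, and either compound symmetry (CS) or AR(1). Effects are in SD units.

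**The plan's own figure.** The section does not say which test, alpha or number of visits gives 85%. Of the variants tried at 120 per arm, the only one within 2 points is a time-averaged group difference over three visits with AR(1) correlation 0.3 and two-sided alpha 0.025:

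- variance of the mean of three visits = (3 + 2(0.3 + 0.3 + 0.09))/9 = 0.487
- standard error = √(2 × 0.487/120) = 0.0901
- 0.30/0.0901 = 3.33 against a critical value of 2.24, giving 86.2% power

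That is not the interaction test.

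**The interaction test.** Degrees of freedom = (2 − 1)(4 − 1) = 3, and the critical chi-square at 0.025 is 9.35. With arm differences δ at the four visits, the noncentrality under CS is

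λ = n/(2(1 − ρ)) × Σ(δ − mean δ)² = 120/1.4 × Σ(δ − mean δ)² = 85.71 × Σ(δ − mean δ)².

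For an effect d at one visit only, or at all three post-baseline visits, Σ(δ − mean δ)² = 0.75 d². For an effect at two of the four visits it is d². AR(1) uses the general quadratic form.

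| True pattern | λ, CS | Significant, CS | Significant, AR(1) |
|---|---|---|---|
| Week 8 only, 0.30 SD | 85.71 × 0.0675 = 5.79 | 39% | 40% |
| Week 8 only, 0.35 SD | 85.71 × 0.0919 = 7.87 | 54% | 55% |
| Week 8 only, 0.50 SD | 85.71 × 0.1875 = 16.07 | 89% | 90% |
| Weeks 8, 16 and 32, 0.30 SD | 85.71 × 0.0675 = 5.79 | 39% | 31% |
| Weeks 16 and 32 only, 0.30 SD | 85.71 × 0.09 = 7.71 | 53% | 36% |

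Under CS the first and fourth rows have the same λ. The test responds identically to a benefit confined to week 8 and to one that lasts through week 32.

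**What the week-8-only results look like at weeks 16 and 32.** In a simulation (CS, 0.30 SD at week 8 only) the interaction was significant in 39% of trials. In 95% of those, neither the week-16 nor the week-32 change contrast showed a PASS benefit at two-sided 0.025.

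**Single-visit contrasts, 0.30 SD, alpha 0.025, correlation 0.3 with baseline.**

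- Change score: standard error √(2 × 2(1 − 0.3)/120) = 0.153, ratio 1.96, power 39%.
- Baseline-adjusted: standard error √(2 × (1 − 0.09)/120) = 0.123, ratio 2.44, power 58%.

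**Error rates.** As written there is one interaction test per primary outcome at 0.025, so the family-wise error is at most 2 × 0.025 = 5%. If two outcomes were instead each read at weeks 16 and 32 at 0.025 without gating, four tests would give 8.5–9.1% (simulation; between-visit correlation 0.5, between-outcome correlation 0.5 down to 0).

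**The case against.** The strongest reply is that the information needed for a sound reading is already planned. Estimates and intervals for the difference in mean change will be reported, the effect-size section adds a standardised difference in change, and the abstract points to differences at post-treatment and follow-up. Any two-sided test is non-directional until its estimate is read, and the sentence says only that one arm is superior, not that PASS is. This stands. A reader might infer that the rule could pass off harm as a PASS benefit, but the reported sign would show it.

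A reader might also infer that the 0.05/2 split leaves the family-wise error inflated. The documents do not support that: the rule as written makes two primary tests at 0.025. The 8.5–9.1% arises only if that rule is set aside and visits are read separately without control.

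The 89–90% figure is a chosen extreme. It needs 0.5 SD at week 8 and exactly nothing at week 16, although the intervention period runs to week 16, and nothing in the protocol predicts that pattern. A crossing pattern (+0.30 SD at week 16, −0.30 SD at week 32) gives 88–89%, but it contains a true week-16 benefit and so does not illustrate the point.

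Finally, the article is condensed and an analysis plan not shown may order the visit contrasts. That excuses missing detail. It does not cover this sentence, because the article itself states a criterion, and a plan that names another would contradict it.

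**Conclusion.** The concern holds in a limited form. The superiority sentence does not match the objective: for both primary outcomes it makes a 3-df interaction decisive, and that test can be significant because of week 8 alone. At 0.30 to 0.35 SD, a week-8-only effect would meet the criterion in 39–55% of trials. The same test finds a sustained 0.30 SD benefit in 31–39%, well short of the stated 85%. The gap to 85% depends on the Sample size section having meant a different test. The time-averaged match is an inference, so the figures do not prove that section wrong on its own terms.

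The percentages assume 120 complete cases per arm, correlation 0.3 under CS or AR(1), and two-sided alpha 0.025. That the test is tied to no visit does not depend on them. Other Objective 1 outcomes have no week-8 visit. Their interaction has 2 df and the week-8 problem does not arise, though no deciding contrast is named there either. This should be fixed; it is not a fatal flaw, because the needed estimates are already planned.

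**What to change.** Replace the sentence. For each primary outcome, let superiority rest on the model-based PASS–TAU difference in change from baseline at week 16 and/or week 32, reported with its sign and confidence interval. Keep the week-8 contrast and the interaction test as supportive.

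If both visits count, control error over them within each outcome's 0.025. The objective ranks neither visit, so the choice is the investigators':

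- fixed sequence, for example week 16 and then week 32;
- alpha split between the two visits;
- a joint 2-df test of weeks 16 and 32, followed by the visit contrasts if it is significant.

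Then restate the power for the chosen contrast, with alpha, sidedness, visit and baseline handling. At 0.30 SD a single visit gives about 39% as a change score and 58% with baseline adjustment.

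No new data are needed. The cost is that one visit becomes conditional or alpha is divided, and that the power statement becomes less favourable, so the change goes beyond one sentence.

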### Trial design

The study is a two-group, parallel randomized controlled trial**.** Patients will be randomly assigned to PASS or TAU, 150 participants per condition. Randomization will be stratified by practice (seven practices) and parental report of ADHD medication usage (yes, no) at time of random assignment. We will request that parents in PASS and TAU report about services they are receiving in the community during the intervention and follow-up periods. Outcome measures pertaining to Objectives 1 and 2 will be administered at baseline, post-treatment (16 weeks after baseline), and follow-up (32 weeks after baseline) from caregivers and teachers. Caregivers, but not teachers, will also be asked to complete a brief set of outcome measures at a mid-treatment time point (8 weeks after baseline). During the follow-up period, families in PASS will no longer receive the PASS intervention, and families in both conditions will have access to behavioral health services integrated into primary care. Family attendance at sessions and adherence to recommended treatment strategies will be assessed continuously during the intervention. Family utilization of behavioral health services in primary care prior to the study, during the intervention period, and during follow up will be monitored to examine the contrast in service delivery between treatment conditions. Subgroups identified by level of socioeconomic resources, caregiver stress, and caregiver health literacy, child clinical characteristics, as well as child medication status at baseline will be delineated to examine whether there are differences in outcome as a function of subgroup. PASS will be provided in the context of the integrated primary care program at our institution. Integrated primary care providers will incorporate PASS sessions into their clinical schedules, deliver PASS to families, and bill for services as they typically do in practice. To promote participant retention in the study, newsletters will be disseminated to caregiver participants on a regular basis.

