#### Treatment as usual (TAU)

The control condition (TAU) includes access to existing integrated behavioral health service in primary care. Services provided to families in primary care during the 16-week intervention period are highly variable. The lag time from referral to first appointment and the availability of follow-up appointments after first visit vary markedly across practices. TAU does not include support from a Community Health Partner. Both conditions will include ongoing pediatric health care informed by AAP guidelines for managing ADHD [19] and facilitated by electronic practice supports, which have been successfully incorporated into the EHR to guide PCPs in implementing ADHD guidelines. Families assigned to TAU may be referred for community-based behavioral health services during the study period.

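### Medication status and practice enter the primary MMRM only as time-constant effects, so the tested difference in change is essentially not adjusted for the stratification factors

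*Protocol article*

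**What the plan says.** The Trial design section states: "Randomization will be stratified by practice (seven practices) and parental report of ADHD medication usage (yes, no) at time of random assignment". That gives 7 × 2 = 14 strata, with 1:1 allocation (Assignment of interventions).

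The Objective 1 analysis section then fixes the following.

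- Responses: "The model will examine intervention effects across four time points (baseline, mid-treatment", followed by post-treatment and follow-up. Baseline is therefore an outcome in the model and not a covariate.
- Fixed effects: "MMRM will include the fixed categorical effects of treatment, time, randomization stratification factor (medication status and primary care practice), and treatment-by-time interaction", then "as well as covariates as indicated". Treatment-by-time is the only interaction named.
- Covariance: "Within-participant error variance–covariance will be assumed to be an unstructured matrix".
- Decision: "A significant time by treatment interaction will indicate that one treatment is superior to the other".
- Reported effect: "the difference in the estimated mean change between groups will be calculated".

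Objective 2 uses the same MMRM approach over three time points. The sensitivity analysis for both objectives is a GEE.

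**The concern.** Stratification factors are normally put in the model so that the tested contrast, and its standard error, reflect the balance that stratification produced. Here the tested contrast is a difference in change from baseline, while the stratum terms are constant over time. They can explain why some children score higher throughout. They cannot explain why some children change more.

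If medication status or practice predicts change, that variation stays in the residual. The standard error is then larger than the true sampling variability under stratified allocation. Both primary outcomes are tested at 0.025 and would lose some power, and so would the Objective 2 measures.

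**Working it through.** **1. Cancellation.** For child i in arm a at visit t, the listed model is Y_it = μ_at + X_i·b + e_it, where X_i holds medication status and practice. Then Y_it − Y_i0 = (μ_at − μ_a0) + (e_it − e_i0), and X_i·b is gone. Write the likelihood as f(changes) × f(baseline given changes). The vector b appears only in the second factor, which has its own free arm-specific intercept and, because the covariance is unstructured, free slopes. With complete data the treatment-by-time estimates therefore come from the first factor alone, as if no strata had been listed.

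**2. Numerical check, complete data.** An unstructured MMRM was fitted by maximum likelihood to simulated data (300 children, 7 practices × medication, correlation 0.3). For one trial the difference in change was:

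| Model | Week 16 (SE) | Week 32 SE |
|---|---|---|
| No stratum terms | −0.2086 (0.1583) | 0.1437 |
| Stratum main effects, as listed | −0.2086 (0.1583) | 0.1437 |
| Stratum-by-time added | −0.2072 (0.1559) | 0.1369 |

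The first two rows agree to about 13 decimals and equal the raw difference in mean change. Over 250 trials in each complete-data scenario the largest discrepancy between them was 0.00000.

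**3. Numerical check, incomplete data.** With 20% missing completely at random, the main effects moved the estimate by 0.007 to 0.010 SD on average (largest shift 0.024 to 0.043). The SE hardly changed (0.1507 against 0.1517, with a 0.5 SD medication effect on change). Under an assumed strong dependence of dropout on arm and medication (true effect −0.30, medication effect on change 0.5 SD), mean estimates were −0.355 with no strata, −0.323 as listed and −0.294 with stratum-by-time. The listed terms then do part of the work.

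**4. The plan's power figure.** The Sample size section gives 85% power for 0.30 SD with 240 evaluable children and autocorrelation 0.3. No formula is named. A time-averaged comparison over three visits with AR(1) correlation comes close: the variance multiplier is [3 + 2(2×0.3 + 0.09)]/9 = 0.487, SE = √(2×0.487/120) = 0.0901, and power = Φ(0.30/0.0901 − 2.241) = 86%. That is a different contrast from the difference in change tested here. The point below does not depend on it.

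**5. Size for the change contrast.** Inputs: 120 per arm, correlation 0.3, alpha 0.025 (taken as two-sided, z = 2.241), and effect 0.35 SD, the lower end of the expected range. The variance of change is 2(1 − 0.3) = 1.4 SD², so SE as written = √(2×1.4/120) = 0.1528. Under stratified allocation the true SE is 0.1528·√(1 − R²).

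- Adjusted power = Φ(0.35/[0.1528·√(1 − R²)] − 2.241).
- Actual two-sided error as written = 2[1 − Φ(2.241/√(1 − R²))].

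| R² (assumed) | True SE | SE too wide by | Actual error as written | Power as written | Power adjusted |
|---|---|---|---|---|---|
| 0 | 0.1528 | 0 | 0.025 | 52% | 52% |
| 5% | 0.1489 | 2.6% | 0.0215 | 52% | 54% |
| 10% | 0.1449 | 5.4% | 0.018 | 52% | 57% |
| 15% | 0.1408 | 8.5% | 0.015 | 52% | 60% |

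**6. What R² might be.** Assume 60% of children are medicated and a within-stratum change variance of 1.4. A medication difference in change of d and a practice SD of s give R² = v/(1.4 + v), with v = 0.24d² + s².

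- d = 0.25, s = 0.15: 0.0375/1.4375 = 2.6%
- d = 0.5, s = 0.3: 0.15/1.55 = 9.7%
- d = 0.8, s = 0.3: 0.2436/1.6436 = 14.8%

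**7. Cross-check over 250 complete-data trials** (300 children, effect 0.30 SD, practice effects −0.3 to +0.3 SD). With a 0.5 SD medication effect on change, mean SE fell from 0.141 to 0.134 and power rose from 47% to 53%. With 0.8 SD, SE fell from 0.145 to 0.134 and power rose from 42% to 47%. With no stratum effect on change, SE was 0.135 against 0.133 while the empirical SD was the same (0.146). About 1% of each SE reduction is therefore an artefact of maximum likelihood and not a gain.

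**The case against.** The strongest reply is that this is a refinement in a condensed article. It calls MMRM the general approach, names the stratification factors as fixed effects, and leaves room through "as well as covariates as indicated". Part of this stands, because the wording does not forbid stratum-by-time terms. But the article does list the model's terms and places the stratification factors among the main effects. Followed as written, the model does not adjust the tested contrast, and the open clause does not supply the missing terms.

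Three further objections stand and limit the point.

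- Nothing in the article quantifies how far the strata predict change. Differencing already removes time-constant stratum differences. If R² is 5% or less, the gain is 2 points or fewer.
- A reader might take "The lag time from referral to first appointment and the availability of follow-up appointments after first visit vary markedly across practices" as evidence of a practice effect on change. It describes access to services within TAU. If anything it suggests that the treatment effect differs by practice, not a practice trend common to both arms. The conceptual framework links medication status to changes in service use and care processes, and to child outcomes only through a proposed mediation path.
- A reader might infer that the primary test is biased or has inflated error, or that stratification is ignored outright. The documents do not support this. With complete data there is no bias and the test is at most mildly conservative. With 20% attrition the cancellation is approximate. The biased scenario in the working needs a dropout pattern that the article nowhere describes, and the missing-data section commits to comparing missingness between arms.

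**Conclusion.** The point holds in a limited form. In the model as listed, medication status and practice have no influence on the difference-in-change estimate or its precision with complete data, and only a small or partial influence under the planned attrition. The tested contrast is therefore essentially unadjusted for the factors used to stratify.

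The consequence is lost efficiency in the conservative direction. It ranges from nothing at R² = 0 to an SE 8.5% too wide, an actual error of about 0.015, and about 8 points of power forgone at R² = 15%. The R² range is an assumption, as are the two-sided alpha and the 0.35 SD effect. The conservative error rate also assumes that the randomisation achieves good balance within strata. The precision gain from adjustment does not rest on that.

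**What to change.** In the Objective 1 analysis section, and by reference Objective 2, list the fixed effects for parent- and child-report outcomes as: treatment, time, treatment-by-time, medication status, practice, medication-status-by-time and practice-by-time, with the treatment contrast averaged over strata. Use the same terms in the sensitivity GEE.

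No new data are needed. The cost is 7 stratum contrasts (1 for medication, 6 for practice) at each post-baseline visit: 7 × 3 = 21 parameters for the two primary outcomes and 7 × 2 = 14 where there is no mid-treatment visit, against about 240 children. The loss is negligible if the strata turn out not to predict change.

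For the exploratory teacher-report outcomes, with about 100 evaluable cases over seven practices, cells are small. There practice-by-time may be omitted and medication-status-by-time kept. The choice should be written down before outcome data are analysed.

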### Sample size

Based on prior research [26, 28, 35], the magnitude of the effect size reflecting the degree of change in response to PASS vs TAU for service use and child outcomes (Objective 1) and care processes (Objective 2) is expected to be the 0.35 to 0.60 SD range. Based on prior research using a similar behavioral intervention [41], we assumed a standard deviation for a single observation = 0.50 and an autocorrelation = 0.3. Projecting an enrollment of 300 participants (150 per condition), and given an expected 20% attrition rate, we expect 240 participants will provide parent-report and child self-report data at baseline and at least one other data collection point. Using statistical methods described below, analytic models will achieve 85% power to detect an effect size as small as 0.30 SD. Given the challenges of collecting data from teachers related to the COVID-19 pandemic, the number of evaluable cases will be well below 240 (estimated to be 100). As such, analyses of teacher-report data will be exploratory. In addition, analyses of mediation (Objective 3) and subgroup effects (Objective 4) will be exploratory.

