### Objective 2 (Evaluate differences between PASS and TAU in changing parenting practices, improving family empowerment in seeking services, and improving caregiver perceptions of team-based care)

MMRM using an ITT approach will be the general analytical approach for testing Objective 2. The analytic model for examining Objective 2 will examine intervention effects across three time points (baseline, post-treatment, follow-up). We will test for significance using a *p* value of 0.025 to be consistent across analyses.

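### The MMRM leaves the arm means free at baseline, so it estimates an unadjusted difference in change and gives up about a third of the achievable precision at the plan's correlation of 0.3

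*Protocol article*

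**What the plan says.** The model is in the protocol article, under the data analysis plan for Objective 1. Baseline is part of the response: "The model will examine intervention effects across four time points (baseline, mid-treatment [parent report of homework performance and behavior compliance only], post-treatment, follow-up"). The fixed effects follow: "MMRM will include the fixed categorical effects of treatment, time, randomization stratification factor (medication status and primary care practice), and treatment-by-time interaction", and the sentence ends "as well as covariates as indicated". On the covariance: "Within-participant error variance–covariance will be assumed to be an unstructured matrix". The decision rule is "A significant time by treatment interaction will indicate that one treatment is superior to the other", and the reported effect is a contrast of changes: "the difference in the estimated mean change between groups will be calculated".

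The Objective 2 section uses the same approach; its model "will examine intervention effects across three time points (baseline, post-treatment, follow-up").

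The Sample size section gives the planning values: "we assumed a standard deviation for a single observation = 0.50 and an autocorrelation = 0.3". It expects 240 evaluable participants out of 300 and claims 85% power for 0.30 SD.

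Neither analysis section names the baseline value of the outcome as a covariate or constrains the arms to start from the same mean. In the Objective 3 section, by contrast, the baseline mediator is a covariate, for precision and because of regression to the mean.

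**The concern.** A treatment main effect plus a full treatment-by-time interaction, with baseline among the time points, gives each arm its own baseline mean. In a randomised trial the true difference at baseline is zero. The model spends information estimating that known quantity and then subtracts the noisy estimate from the post-treatment difference.

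How much this costs depends on the correlation between baseline and outcome. Below 0.5, subtracting baseline makes the comparison noisier than ignoring baseline altogether, and the plan assumes 0.3. Any chance imbalance at baseline passes in full into the complete-data estimate, whereas an adjusted analysis passes on only the part that baseline does not predict. At stake is precision on the two primary outcomes and on every other outcome analysed with this model.

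**Working it through.** **Inputs.** From the Sample size section: correlation 0.3, 240 evaluable (taken as 120 per arm), 85% power at 0.30 SD, and an expected effect of 0.35 to 0.60 SD. From the Objective 1 section: 0.025 per primary outcome, taken as two-sided. Everything is in SD units, so the SD of 0.50 cancels. Assumption: 0.3 is the correlation between any two visits (compound symmetry). The article says only autocorrelation, so a first-order autoregressive reading is also shown.

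**1. The plan's own 85%.**
- Difference in change at one visit: SE = √(2 × 1.40/120) = 0.153. Power for 0.30 SD is 50% at 0.05 and 39% at 0.025. This does not reproduce 85%.
- Average of three post-baseline visits, baseline unused, autoregressive 0.3: variance (3 + 2(0.3 + 0.3 + 0.09))/9 = 0.487. Power at 0.025 is 86%, which is close to the stated figure.
- The same average under compound symmetry: variance (1 + 2 × 0.3)/3 = 0.533. Power is 83% at 0.025 and 89% at 0.05.

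So 85% is approached only by a time-averaged contrast, which is not the effect the analysis section reports.

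**2. Variance per arm at one post-baseline visit, complete data.**
- Difference in change: 2(1 − ρ) = 2 × 0.7 = 1.40 SD².
- Post-treatment value alone: 1.00 SD².
- Baseline adjusted: 1 − ρ² = 1 − 0.09 = 0.91 SD².
- Ratio adjusted to change: (1 + ρ)/2 = 0.65, so 35% of the precision is lost. The planned SE is √(1.40/0.91) = 1.24 times the adjusted one.
- Sample-size equivalent: 240 × 1.40/0.91 = 369.

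**3. Consequences with 120 per arm.**

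| | Difference in change | Baseline adjusted |
|---|---|---|
| SE (SD units) | 0.153 | 0.123 |
| 95% CI half-width, 1.96 × SE | 0.299 | 0.241 |
| Power for 0.30 SD at 0.025 | 39% | 58% |
| Power for 0.35 SD at 0.025 | 52% | 73% |

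**4. With attrition.** Suppose 150 per arm have a baseline and 30 of them have nothing later. The likelihood fit of the planned model then has variance 2 × [0.91/120 + (1 − 0.3)²/150] = 0.0217. The common-baseline model has 2 × 0.91/120 = 0.0152. The loss is 30%. With monotone dropout (140, 130 and 120 per arm at the three visits) it is 32% at week 16 and 30% at week 32.

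**5. The interaction test itself.** Take a constant 0.30 SD effect at all three post-baseline visits, complete data and compound symmetry, on 3 degrees of freedom.
- Noncentrality as planned: 0.09 × 60/0.7 × 3/4 = 5.79. Power at 0.025 is 39%.
- Noncentrality with a common baseline: 0.09 × 60 × 3/(0.7 + 3 × 0.21) = 12.18. Power at 0.025 is 77%.

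**6. Sensitivity to the correlation.** The loss is (1 − ρ)/2: 35% at 0.3, 25% at 0.5 and 15% at 0.7. On the autoregressive reading, the baseline correlation is 0.09 at week 16 and 0.027 at week 32. The loss is then 45% and 49% on complete data, and 40% to 43% with dropout.

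**The case against.** **The model is valid.** Under randomisation the planned contrast is unbiased, its type I error is correct, and it matches the change-based effect the article intends to report. That stands: this is an efficiency defect. A cheaper route to the same target is still worth taking, because the model is stated explicitly and is not merely left unmentioned.

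**The covariate list is open, and a separate analysis plan may settle it.** The closing phrase of the fixed-effects sentence could admit further terms. It names no baseline adjustment, however, and in this model baseline is already a response. As written, the document fixes the inefficient form.

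**The size rests on one planning value.** The 0.3 comes from an earlier study, with no structure or interval given, and some outcomes may correlate more strongly. The article quotes a test–retest value of 0.77 for the Family Empowerment Scale. If that applied here, the saving would be 1 − 1.77/2 = 11.5% of variance, about 6% of the SE. This stands as a limit on the size for individual outcomes, but the gain stays positive at any correlation below 1.

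**Complete data are assumed in the headline.** This is correct, and the working gives 30% to 32% with attrition.

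**A common baseline mean needs baselines taken before allocation.** The article places parent and child baseline at the consent visit (Recruitment; Data collection and management) and randomisation after consent (Allocation concealment mechanism). The baseline medication report sets the stratum (Medication status). It does not say in so many words that every questionnaire was finished before the unblinded allocation was disclosed, so the sponsor should confirm it.

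**Conclusion.** The concern holds. As written, the model estimates a difference in change from an unconstrained baseline. At the plan's correlation of 0.3 this loses 35% of the achievable precision on complete data and 30% to 32% with the planned attrition. These figures take 0.3 as the correlation between baseline and outcome; the loss is larger on an autoregressive reading and smaller if the true correlation is higher. The power figures also assume two-sided 0.025 and 120 per arm observed at the visit.

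The change should be made, but the planned analysis is not invalid without it. Adjustment alone does not bring single-visit power for 0.30 SD up to the stated 85%.

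**What to change.** Amend the model statement for Objectives 1 and 2 before outcomes are analysed, in one of two ways:

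- a constrained longitudinal model with all visits as responses, a common baseline mean, treatment-by-visit terms at post-baseline visits only, and no treatment effect at baseline; or
- post-baseline visits as responses, with baseline and baseline-by-time as covariates.

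Keep the stratification factors and the unstructured covariance. Replace the interaction criterion with the post-baseline treatment terms, so that the stated test matches the new parameterisation.

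Apply this to all parent- and child-reported outcomes, after confirming that their baselines were completed before allocation was disclosed. Teacher baselines are collected after consent, and allocation may already be known by then. For these, apply it only to ratings completed before PASS began.

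The cost is about one line of model code and no new data. For outcomes with a pre-allocation baseline there is no statistical downside.
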